## 12. DISCONTINUATION OF VACCINATIONS AND/OR WITHDRAWAL FROM STUDY

### 12.1 Discontinuation of Vaccinations

Any discontinuation or planned discontinuation from further vaccinations will be discussed with the Sponsor. Volunteers will be discontinued from further vaccination for any of the following reasons:

1. Pregnancy
2. Intercurrent HIV Infection
3. Use of systemic corticosteroids, immunosuppressive, antiviral, anticancer, anti-tuberculosis or other medications considered significant by the investigator. Note: Volunteers requiring chronic corticosteroids (> 2 weeks) or long term therapy will not receive any further vaccinations.
4. A disease or condition or an adverse event that may develop, regardless of relationship to the Investigational Product, if the Principal Investigator or designee is of the opinion that further study vaccinations will jeopardize the safety of the volunteer
5. Anaphylaxis, bronchospasm, laryngeal oedema, convulsions or encephalopathy following study vaccinations
6. Life-threatening adverse event following study vaccination unless not related to the Investigational Product and fully resolved

7. Any immediate hypersensitivity reaction judged to be related to the Investigational Product, if the Principal Investigator or designee is of the opinion that further study vaccinations will jeopardize the safety of the volunteer
8. Volunteer's request to discontinue further vaccination

The following are parameters that require resolution and/or review of clinical history by the Principal Investigator or designee and consultation with the Medical Monitor, prior to continuation of study vaccination(s):

1. Any of the following abnormal laboratory parameters that are known at the time of vaccination:

*Haematology*

- Haemoglobin  $\leq 9.0$  g/dL **or**  $\leq 5.55$  mmol/L
- Absolute Neutrophil Count (ANC):  $\leq 1000/\text{mm}^3$  **or**  $\leq 1.0 \times 10^9/\text{L}$
- Absolute Lymphocyte Count (ALC):  $\leq 500/\text{mm}^3$  **or**  $\leq 0.5 \times 10^9/\text{L}$
- Platelets:  $\leq 90,000 \geq 550,000/\text{mm}^3$  **or**  $\leq 90 \times 10^9 \geq 550 \times 10^9/\text{L}$

*Chemistry*

- Creatinine:  $>1.4 \times \text{ULN}$
- AST:  $\geq 2.6 \times \text{ULN}$
- ALT:  $\geq 2.6 \times \text{ULN}$

2. Receipt of inactivated/killed/subunit vaccines (non-HIV) or immunoglobulin within the previous 14 days or planned receipt within 14 days after vaccination with Investigational Product
3. Receipt of live attenuated vaccines within the previous 60 days or planned receipt within 60 days after vaccination with Investigational Product
4. A Grade 3 or 4 local reactogenicity involving the major part of the injected arm circumference
5. If the use of a short tapering course ( $<2$  weeks) of corticosteroids is required, the study vaccinations may be continued after a 4-week washout period, provided that the medical condition requiring this therapy has completely resolved and in the opinion of both the site investigator and Medical Monitor, the continuation of the study vaccinations will not jeopardize the safety of the volunteer.

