### 5.2.4 Exclusion Criteria

1. Confirmed HIV-1 or HIV-2 infection;
2. Any clinically relevant abnormality on history or examination including history of immunodeficiency or autoimmune disease; use of systemic corticosteroids (the use of topical or inhaled steroids is permitted); immunosuppressive, anti-cancer, anti-tuberculosis or other medications considered significant by the investigator within the previous 6 months;
3. Any clinically significant acute or chronic medical condition that is considered progressive, or in the opinion of the investigator, makes the volunteer unsuitable

- for participation in the study;
4. Reported risky behaviour for HIV infection within 12 months prior to vaccination, as defined by:
    - Unprotected sexual intercourse with a known HIV-infected person, a partner known to be at high risk of HIV infection or a casual partner (i.e., no continuing established relationship)
    - Engaged in sex work
    - Frequent excessive daily alcohol use or frequent binge drinking or chronic marijuana or any other use of use of illicit drugs
    - History of newly-acquired syphilis, gonorrhoea, non-gonococcal urethritis, HSV-2, chlamydia, pelvic inflammatory disease (PID), trichomonas, mucopurulent cervicitis, epididymitis, proctitis, lymphogranuloma venereum, chancroid, or hepatitis B;
    - Three or more sexual partners
  5. If female, pregnant or planning a pregnancy within 4 months after last study vaccination; or lactating;
  6. Asthma requiring high-dose oral or inhaled corticosteroids;
  7. Bleeding disorder that was diagnosed by a physician (e.g., factor deficiency, coagulopathy or platelet disorder that requires special precautions) (Note: A volunteer who states that he or she has easy bruising or bleeding, but does not have a formal diagnosis and has IM injections and blood draws without any adverse experience, is eligible);
  8. History of splenectomy;
  9. Any of the following abnormal laboratory parameters listed below:
    - Haematology
      - Haemoglobin  $\leq 9.0$  g/dL **or**  $\leq 5.55$  mmol/L
      - Absolute Neutrophil Count (ANC):  $\leq 1000/\text{mm}^3$  **or**  $\leq 1.0 \times 10^9/\text{L}$
      - Absolute Lymphocyte Count (ALC):  $\leq 500/\text{mm}^3$  **or**  $\leq 0.5 \times 10^9/\text{L}$
      - Platelets:  $\leq 90,000 \geq 550,000/\text{mm}^3$  **or**  $\leq 90 \times 10^9 \geq 550 \times 10^9/\text{L}$
    - Chemistry
      - Creatinine:  $>1.4$  x upper limit of normal (ULN)

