## **6.2 Vaccination Visits**

*Prior to the first vaccination, study staff will:*

- Answer any questions about the study
- Review the Informed Consent Document
- Review screening safety laboratory data
- Administer HIV risk assessment
- Conduct family planning counselling as per site-specific procedures and ensure compliance with respective contraceptive method
- Review interim medical history
- Collect concomitant medication information
- Perform a symptom-directed physical examination (Refer to Section 7.2)
- Baseline assessment of local and systemic signs and symptoms (this includes an examination of vaccination site)
- Collect specimens for all tests as indicated in the Schedule of Procedures (Appendices A-B). Obtain pregnancy test results prior to vaccination.

The volunteer will be assigned an allocation number according to the instructions specified in the Study Operations Manual (SOM).

The Investigational Product will be administered as specified in Section 8.4, Administration of Investigational Product and according to the instructions specified in the SOM.

Study staff will observe volunteers closely for at least 30 minutes after each vaccination for any acute reactogenicity. At the end of the observation period study staff will:

- Record vital signs (pulse, respiratory rate, blood pressure and temperature)
- Assess any local and systemic reactogenicity
- Assess any other adverse events
- Ask volunteer to complete EP tolerability assessment (unless volunteer is in Group 5, in which case they will complete the EP tolerability assessment following their Month 4 vaccination only)

*Subsequent Vaccination Visits:*

Study staff will perform the same procedures as above with the following exceptions:

- Review the routine safety laboratory parameters (Section 9.1.6), as appropriate, from the previous visit prior to each vaccination. If a volunteer has an abnormal laboratory value that is known at the time of vaccination, follow the specified guidelines (Section 12.0)
- Conduct pre HIV-test counselling if an HIV test is scheduled (see Appendices A-B) or clinically indicated
- Provide post-test counselling if the results of a prior HIV test are being communicated to the volunteer
- Do not conduct EP tolerability assessment following vaccinations that do not use EP

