### **17.1 Protocol Safety Review Team**

The Protocol Safety Review Team (PSRT) will be formed to monitor the clinical safety data. During the vaccination phase of the trial, the PSRT will review clinical safety data on a weekly basis. An *ad hoc* PSRT review meeting will occur if any of the members of the PSRT requests a special review to discuss a specific safety issue or as specified in the Study Operations Manual.

The PSRT will consist of the IAVI Medical Monitor(s) and PI or designee from each clinical team. An IAVI Medical Monitor will be the PSRT Chair. *Ex officio* members will include the IAVI CMO, IAVI Medical Safety Monitor and representatives from Profectus Biosciences Inc. and Ichor Medical Systems, Inc.

Additional PSRT participants may include the following, as needed:

- Co-investigators and CRC senior clinical research nursing staff
- Laboratory directors
- Data management, study statistician and regulatory staff

The Terms of Reference for PSRT and procedures to be followed are detailed in the SOM.

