| Laboratory Specimens                                                                          |        |     |     |     |     |     |     |     |     |     |     |     |     |                |      |      |      |      |      |                |      |                        |
| HIV test                                                                                      | X      |     |     |     |     |     |     |     |     |     |     |     |     | X  |      |      |      |      |      | X  |      | X          |
| Hep BsAg, anti-HepC, active syphilis                                                          | X      |     |     |     |     |     |     |     |     |     |     |     |     |                |      |      |      |      |      |                |      |                        |
| Haematology (+ plasma storage)                                                                | X      |     |     |     |     | X   |     |     |     | X   |     |     |     | X              |      | X    |      |      | X    | X              | X    | X                      |
| Clinical Chemistry (+ serum storage)                                                          | X      |     |     |     |     | X   |     |     |     | X   |     |     |     | X              |      | X    |      |      | X    | X              | X    | X                      |
| Immunology (CD4, CD8)                                                                         |        | X   |     |     |     |     |     |     |     |     |     |     |     |                |      |      |      |      |      |                |      | X                      |
| Urinalysis                                                                                    | X      | X   |     |     |     | X   |     |     |     | X   |     |     |     |                |      | X    |      |      |      |                |      | X                      |
| Pregnancy Test (all female volunteers)                                                        | X      | X   |     |     |     | X   |     |     |     | X   |     |     |     |                |      | X    |      |      |      |                | X    | X                      |

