| Comment: The decrease is a decrease from baseline                                                                                                                                                                                                                                                                                                                                           |                                                                                                                    |                                                                                                                  |                                                                                                         |                                                                |
| Infant†, 36 – 56 days
(HIV POSITIVE OR NEGATIVE)                                                                                                                                                                                                                                                                                                               | 8.5 – 9.4 g/dL
5.24 – 5.86 mmol/L                                                                        | 7.0 – 8.4 g/dL
4.31 – 5.23 mmol/L                                                                      | 6.0 – 6.9 g/dL
3.72 – 4.30 mmol/L                                                             | < 6.00 g/dL
< 3.72 mmol/L                            |
| Infant†, 22 – 35 days
(HIV POSITIVE OR NEGATIVE)                                                                                                                                                                                                                                                                                                               | 9.5 – 10.5 g/dL
5.87 – 6.54 mmol/L                                                                       | 8.0 – 9.4 g/dL
4.93 – 5.86 mmol/L                                                                      | 7.0 – 7.9 g/dL
4.34 – 4.92 mmol/L                                                             | < 7.00 g/dL
< 4.34 mmol/L                            |

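### The haemoglobin trigger for Medical Monitor consultation before the next dose (Section 12.1) is an absolute level only, so a Grade 3 fall from baseline can miss it

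*Protocol*

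**What the plan says.** The second list in Protocol Section 12.1 sets out "parameters that require resolution and/or review of clinical history by the Principal Investigator or designee and consultation with the Medical Monitor" before vaccination continues. Item 1 of that list covers "Any of the following abnormal laboratory parameters that are known at the time of vaccination", and its haemoglobin line is ≤9.0 g/dL (≤5.55 mmol/L). The same figures stand in exclusion criterion 9 of Section 5.2.4, under "Any of the following abnormal laboratory parameters listed below".

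Appendix C grades haemoglobin in HIV-negative adults in two alternative ways, by level or by fall. Grade 3 is 7.0–8.9 g/dL, or any decrease of ≥4.5 g/dL. A comment under the row adds: "The decrease is a decrease from baseline".

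Section 6.2 links the two parts at each later dosing visit: "If a volunteer has an abnormal laboratory value that is known at the time of vaccination, follow the specified guidelines", with a pointer to Section 12. Section 10.5 sends known adverse events and abnormal laboratory values to the same place.

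**The concern.** A screening limit has to be absolute, because no baseline exists yet. Once volunteers have been dosed, a change from baseline can be measured, and the protocol's own grading table treats a large one as severe. Section 12.1 carries the screening limit over unchanged, so it cannot respond to a large fall that stops above 9.0 g/dL.

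What is at stake is dosing safety for the individual volunteer. With such a fall on record, the next dose could be given without the consultation that Section 12.1 requires for the values it lists. The event would still be recorded, graded and counted, so the safety endpoints and their analysis do not change.

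**Working it through.** **Inputs.** The 12.1 limits come from the second list, item 1. The grades come from the Appendix C laboratory tables, using the adult rows and, for haemoglobin and lymphocytes, the HIV-negative rows. Sampling days come from the haematology rows of Appendices A and B.

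**Step 1: does each 12.1 limit catch every Grade 3 value of its parameter?**

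| Parameter | 12.1 limit | Appendix C Grade 3 | All Grade 3 caught? |
|---|---|---|---|
| ANC (/mm³) | ≤1000 | 500–749 | Yes |
| ALC (/mm³) | ≤500 | 350–499 | Yes |
| Low platelets (/mm³) | ≤90,000 | 25,000–49,999 | Yes |
| Creatinine (× ULN) | >1.4 | 1.9–3.4 | Yes |
| AST, ALT (× ULN) | ≥2.6 | 5.1–10.0 | Yes |
| Haemoglobin, by level (g/dL) | ≤9.0 | 7.0–8.9 | Yes |
| Haemoglobin, by fall (g/dL) | none | ≥4.5 | Not always |

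**Step 2: when does a Grade 3 fall miss the list?** The smallest Grade 3 fall leaves haemoglobin at baseline − 4.5. It escapes if baseline − 4.5 > 9.0, that is, if baseline > 13.5 g/dL. From 13.5 or below, any fall of 4.5 or more ends at 9.0 or lower and is caught by level.

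**Step 3: how wide is the gap?** Missed Grade 3 values run from 9.1 to baseline − 4.5. The fall needed to reach the present limit is baseline − 9.0. The baselines are illustrative, because the protocol gives no haemoglobin distribution.

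| Baseline (g/dL) | After a fall of 4.5 | Grade by level alone | Missed Grade 3 values | Fall needed to reach 9.0 |
|---|---|---|---|---|
| 13.0 | 8.5 | 3 | none | 4.0 |
| 13.5 | 9.0 | 2 | none | 4.5 |
| 14.0 | 9.5 | 2 | 9.1–9.5 | 5.0 |
| 15.0 | 10.5 | 1 | 9.1–10.5 | 6.0 |
| 16.0 | 11.5 | not graded | 9.1–11.5 | 7.0 |

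As a worked case, 15.0 to 10.4 is a fall of 4.6 g/dL. That is Grade 3 by fall and Grade 1 by level (10.0–10.9), and it is not on the 12.1 list.

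**Step 4: could the fall be known before a dose?** Samples drawn on a dosing day are counted as known only for the next dose.

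- Groups 1–3 have haematology at screening, D28, D56, D84 and D168. A post-vaccination fall can therefore be known before the D56 dose (D28 sample) and before the D168 dose (D56 and D84 samples).
- Groups 4–5 have it at screening, D0, D14, D28 and D112. A fall can be known before the D112 dose (D14 and D28 samples).

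**Step 5: does other text require the consultation?** I found none. Section 12.1, first list, item 4 rests on the investigator's opinion. Section 17.3 has no laboratory pausing criterion. Section 12 has no general rule for Grade 3 laboratory values.

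**The case against.** The strongest reply is that nothing here is contradicted. Section 12.1 never claims to follow Appendix C or to mean Grade 3 and above, and the appendix is a grading guideline, not a dosing rule. The listed limits fall at different points on the grading scale: platelets inside Grade 2, AST and ALT at the start of Grade 2, ALC at the edge of Grades 2 and 3. Other routinely measured quantities with a Grade 3 category, such as leucocytes and proteinuria, are not listed at all. On this view the list simply reapplies the screening limits, which is a coherent and simple rule.

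There is also softer cover. Section 6.2 tells staff: "Review the routine safety laboratory parameters (Section 9.1.6), as appropriate, from the previous visit prior to each vaccination". Item 4 of the first list lets the investigator stop dosing. Under Section 17.1, "the PSRT will review clinical safety data on a weekly basis" during the vaccination phase, with a Medical Monitor in the chair. The shortest interval from a usable sample to the dose is 28 days (D28 to D56), about four weekly reviews. Procedures in the Study Operations Manual, which is not available here, may add more.

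Most of this stands, and it limits the size of the point. The list is not a complete Grade 3 net, and a fall of this kind would probably be noticed. But none of the cover is a required check on the individual volunteer before the dose. The Section 6.2 review is qualified, and read literally it looks only one visit back. In Groups 1–3 the visits just before the D56 and D168 doses are D42 and D140, and neither has haematology. Nor does simplicity explain leaving out a criterion that the protocol already defines and for which it already collects the data.

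**Conclusion.** The point holds, at minor severity. From a baseline above 13.5 g/dL, a Grade 3 haemoglobin fall that stays above 9.0 g/dL does not trigger the mandatory Medical Monitor consultation, and haemoglobin is the only parameter on the list with this property. The gap is narrow: one pattern in one parameter, with partial cover elsewhere and no effect on any endpoint or analysis.

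The frequency cannot be estimated from the protocol, and such falls should be rare in healthy adults. The conclusion assumes that Appendix C is applied as written for HIV-negative adults and that scheduled results reach the site before the next dose.

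**What to change.** In the second list of Section 12.1, item 1, extend the haemoglobin line with *or a fall of ≥4.5 g/dL from baseline*. Appendix C pairs this with >2.79 mmol/L; by its conversion factor, 4.5 × 0.6206 = 2.79.

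Define baseline as the last haemoglobin before the first vaccination. That is the screening value in Groups 1–3, which have no D0 haematology, and the D0 value in Groups 4–5. Leave exclusion criterion 9 unchanged.

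The cost is one line in a protocol amendment. No sample or visit is added, because the values are already collected. The downside is an occasional extra consultation before a dose.

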      - AST:  $\geq 2.6$  x ULN
      - ALT:  $\geq 2.6$  x ULN
    - Urinalysis: clinically significant abnormal dipstick confirmed by microscopy
      - Protein 2+ or more
      - Blood 2+ or more (not due to menses);
  10. Receipt of live-attenuated vaccine within the previous 60 days or planned receipt within 60 days after vaccination with Investigational Product; or receipt of other vaccine, allergy treatment with antigen injections or tuberculin skin test within the previous 14 days or planned receipt within 14 days after vaccination with Investigational Product;
  11. Receipt of blood transfusion or blood-derived products within the previous 3 months;
  12. Participation in another clinical trial of an Investigational Product currently, within the previous 3 months or expected participation during this study;
  13. Prior receipt of another investigational HIV vaccine candidate (Note: receipt of

placebo in a previous HIV vaccine trial will not exclude a volunteer from participation if documentation is available and the Medical Monitor gives approval);

14. History of severe local or systemic reactogenicity to vaccines (e.g., anaphylaxis, respiratory difficulty, angioedema);
15. Positive for Hepatitis B surface antigen (HbsAg), positive for antibodies to Hepatitis C virus (HCV) or active syphilis;
16. Psychiatric condition that precludes compliance with the protocol. Specifically excluded are persons with psychoses within the past 3 years, ongoing risk for suicide, or history of suicide attempt or gesture within the past 3 years.
17. History of allergy or hypersensitivity to bupivacaine or any amide-type (local) anesthetics, such as lidocaine (Xylocaine®), mepivacaine (Polocaine®/Carbocaine®), etidocaine (Duranest®), bupivacaine (Marcaine®), or prilocaine or known hypersensitivity to any component of the products tested
18. History of allergy or hypersensitivity to latex
19. Chronic skin problems such as eczema or psoriasis
20. Presence of an implantable device [e.g. Automated Implantable Cardioverter-Defibrillator (AICD), pacemaker, {pain} medication administration pumps]
21. Current use of any electronic stimulation device, such as cardiac demand pacemakers, automatic implantable cardiac defibrillator, nerve stimulators, or deep brain stimulators.

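### Section 12.1 repeats the seven blood limits of exclusion 9 as re-vaccination checks but omits its two urine limits, so a confirmed urine finding that bars entry needs no Medical Monitor consultation before the next dose

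*Protocol*

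**What the plan says.** **At entry.** Protocol Section 5.2.4, item 9 excludes volunteers on four haematology values (haemoglobin, neutrophils, lymphocytes, platelets), three chemistry values (creatinine, AST, ALT) and two urine findings. The urine block is headed "Urinalysis: clinically significant abnormal dipstick confirmed by microscopy". It lists "Protein 2+ or more" and blood at the same level unless menses explain it.

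**Before later doses.** The second list in Section 12.1 names items that "require resolution and/or review of clinical history by the Principal Investigator or designee and consultation with the Medical Monitor" before vaccination continues. Item 1, "Any of the following abnormal laboratory parameters that are known at the time of vaccination", has a haematology block and a chemistry block and no urinalysis block.

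**How staff reach that list.** Section 6.2 tells staff to review the routine safety laboratory parameters of Section 9.1.6, as appropriate, before each later dose. It sends any known abnormal laboratory value to Section 12, and Section 10.5 does the same. Section 9.1.6 counts urinalysis among the routine parameters.

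**What else Section 12.1 offers.** First list, item 4 covers "A disease or condition or an adverse event that may develop, regardless of relationship to the Investigational Product", but acts only if the investigator or designee thinks further doses would jeopardize the volunteer's safety. The section opens with "Any discontinuation or planned discontinuation from further vaccinations will be discussed with the Sponsor".

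**The concern.** The sponsor judged nine laboratory findings serious enough to keep a healthy volunteer out of the trial. For seven of them, the same value known before a later dose brings in a second medical opinion. For the two urine findings it does not, although urine is tested on the same vaccination days and the protocol directs staff to Section 12 with the result. No reason for the difference is given.

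What is at stake is how an individual volunteer is handled. A site could give the next dose after a confirmed, clinically significant 2+ protein or blood result without having to consult anyone outside the site first.

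**Working it through.** No sample size, power or error rate is involved, and the plan states no figure to reproduce. The check is a line-by-line comparison followed by a count of the doses concerned.

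**1. The two lists (Section 5.2.4 item 9 against Section 12.1, second list, item 1)**

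| Parameter | Exclusion 9 | 12.1 item 1 | Appendix C at that limit |
|---|---|---|---|
| Haemoglobin | ≤ 9.0 g/dL | same | lowest Grade 2 value (9.0–9.9) |
| Neutrophils | ≤ 1000/mm³ | same | lowest Grade 1 value (1,000–1,300) |
| Lymphocytes | ≤ 500/mm³ | same | lowest Grade 2 value (500–599) |
| Platelets | ≤ 90,000 or ≥ 550,000/mm³ | same | low limit inside Grade 2 (50,000–99,999); no row for high |
| Creatinine | > 1.4 × ULN | same | start of Grade 2 (1.4–1.8) |
| AST | ≥ 2.6 × ULN | same | start of Grade 2 (2.6–5.0) |
| ALT | ≥ 2.6 × ULN | same | start of Grade 2 (2.6–5.0) |
| Urine protein | 2+ or more | absent | start of Grade 2 (random collection, 2–3+) |
| Urine blood | 2+ or more, not menses | absent | graded by microscopy, no dipstick grade |

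Exclusion 9 has 4 + 3 + 2 = 9 parameters and 12.1 item 1 has 4 + 3 + 0 = 7. The difference is exactly the urinalysis block.

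**2. Can a urine result be known before a later dose?**

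- Appendix A (Groups 1–3) schedules urinalysis at screening and on D0, D28, D56, D168 and D336. Vaccinations are on D0, D28, D56 and D168.
- Appendix B (Groups 4–5) schedules it at screening and on D0, D112 and D336. Vaccinations are on D0 and D112.

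Every later vaccination therefore follows a urine sample planned for the previous vaccination day.

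**3. How many doses are concerned at planned size (15 volunteers per group, 12 vaccine and 3 placebo)?**

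- Later doses: 45 × 3 + 30 × 1 = 165
- Vaccine: 36 × 3 + 24 × 1 = 132
- Placebo: 9 × 3 + 6 × 1 = 33
- Previous urine planned 28 days earlier (D0 to D28, D28 to D56): 45 + 45 = 90 doses
- Previous urine planned 112 days earlier (D56 to D168, D0 to D112): 45 + 30 = 75 doses

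**4. Does another rule require a second opinion before the dose?**

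- First list, item 4 of 12.1 rests on the investigator's opinion.
- The duty to discuss with the Sponsor applies to stopping vaccinations, not to a decision to continue.
- Table 9.1.6-1 requires further tests after a clinically significant dipstick result, but no consultation.
- The PSRT, chaired by a Medical Monitor, reviews clinical safety data weekly during the vaccination phase (17.1). The SRB sees laboratory adverse events that are confirmed on retest and judged related and/or clinically significant (17.2.1). Neither review is a condition for an individual dose.
- The creatinine trigger acts on creatinine only.

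None of these makes Medical Monitor consultation mandatory for a urine finding.

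**The case against.** **No stated rule is broken.** The protocol never says that 12.1 mirrors exclusion 9, and entry and re-dosing criteria often differ. Other entry bars, such as recent transfusion, syncope or hepatitis markers, have no named counterpart in 12.1 either. This stands as far as it goes: the point is an inconsistency, not a contradiction. But hepatitis and syphilis tests are scheduled at screening only, whereas urinalysis is repeated at every vaccination visit, and 12.1 takes over the rest of the exclusion 9 laboratory list limit for limit.

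**Section 12 is not silent.** A reader might infer that a urine abnormality has no rule at all. The documents do not support that. Under 10.1 an abnormal laboratory finding can be an adverse event, and first list, item 4 then applies. What is missing is only the mandatory consultation.

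**Severity grade.** A reader might argue that 2+ protein is Grade 2, like the AST and ALT triggers, and so must be treated alike. The table above shows why this fails. The neutrophil trigger reaches into Grade 1. The haemoglobin, lymphocyte and low-platelet triggers leave part of Grade 2 uncovered, so an absolute haemoglobin of 9.1–9.9 g/dL needs no consultation. High platelets have no grade, and neither does dipstick blood. Section 12.1 does not follow Appendix C grades consistently, so the case rests on the mismatch with entry alone.

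**The practical gap is small.** With 28 planned days between the earlier urine and the next dose, 28 / 7 = 4 weekly PSRT reviews fall in between. This stands as mitigation. It gives the Medical Monitor a route to the data but does not tie the dose to a consultation.

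**The entry wording is awkward to copy.** Microscopy can confirm red cells but does not measure protein. This stands, and the fix allows for it.

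**Conclusion.** The point holds as a minor volunteer-safety inconsistency. Section 12.1 carries over 7 of the 9 laboratory parameters of exclusion 9, and both omitted parameters are urinary. A volunteer with a clinically significant, confirmed urine finding that would have barred entry can receive another dose on the investigator's opinion alone, with weekly PSRT review and the creatinine trigger as partial cover.

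The 165 later doses show where the rule could apply. A reader might take the figure as a measure of risk, but the documents give no frequency of confirmed 2+ findings, and for 75 of these doses the previous vaccination-day urine is 112 days old. Nor does the omission affect sample size, power, endpoints or the primary analysis.

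The conclusion assumes that results from the previous vaccination day are available before the next one, and that the omission was not deliberate. The protocol states no reason for it.

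**What to change.** Add a third block to Section 12.1, second list, item 1, for example:

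> *Urinalysis, clinically significant and confirmed:* protein 2+ or more (confirmed on repeat or quantitative test); blood 2+ or more, not due to menses (confirmed by microscopy).

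The investigator still judges clinical significance, and the Medical Monitor is consulted once that judgement is made. Sections 6.2 and 10.5 already point to Section 12, and neither they nor Appendix C needs to change. If the omission is intended, one sentence saying so would settle the matter.

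No scheduled visit or routine sample is added. The cost is an occasional Medical Monitor consultation, repeat urine test or short dosing delay, at a frequency the documents do not give.
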